### Sampling and randomization

First, all female employees of the health centers will be invited to participate in the study using an announcement. Second, women will be screened for having moderate-to-severe PMS. Third, after a run-in period, primary evaluation of study subjects, and obtaining written informed consent, women who had our eligibility criteria will be randomly assigned to two groups (intervention and control) by using the permuted random blocking method with four and six blocks. Considering that two groups will be studied, four and six blocks in a randomly varied order are utilized and each group is assigned a letter (A: intervention group; B: control group). Since we have a list of all eligible women, the formation of permuted blocks and random allocation of individuals to two groups of intervention and control will be determined prior to the initiation of the research. Indeed, block size of 4 and 6 in a randomly varied order is used to conceal the allocation sequence.

In order to hide the allocation sequence, the type of intervention is written on the cards based on it, and placed in envelopes in a matte package numbered from 1 to 140. In this case, the person who receives intervention code 1 completes a questionnaire with the same code. The assignment of participants to their allocations will be done by an independent healthcare provider. Due to the nature of the study intervention, modification of random allocation during the study and blinding of study participants and outcome evaluators is almost impossible. Although the content of the intervention will be delivered online using the social media platform and blinding is difficult, we tried to maintain the confidentiality of data through coding of study subjects and not asking their identity.

### Intervention

The content of the intervention will be based on the principles of CBT and will be delivered online using the social media platform WhatsApp (Table 1). The intervention lasts for eight consecutive weeks, and its components are divided into 14 individual sections. It commences with an introductory section and ends with one on relapse prevention. The rest of the sections are divided into two categories: cognitive strategies and suggestions for behavioral lifestyle changes. Consequently, except for the initial and the final week, participants work on two parallel sections each week. For these sections, an approximate working time of 5 h per week is recommended.

**Table 1 Tab1:**
[figure not shown]
Contents of the CBT-based treatment for the intervention group

The first part includes psychoeducation about PMS/PMDD, its causes, and treatment. The cognitive strategy section provides information and strategies for identifying and correcting ineffective thoughts, especially PMS-specific cognitions, misbehaviors, and misconceptions. The sections cover suggestions for lifestyle changes, such as stress reduction, exercise, and a balanced diet. In the final section, a summary is provided, along with a plan to sustain the benefits and prevent relapse. All sections include practical exercises for applying and practicing the theoretical content. Additional audio files are provided to facilitate the performance of these exercises, such as an advanced muscle relaxation training program or an audio instructional exercise to gather thoughts related to PMS. Textual information and audio files are delivered through social networks. Weekly feedback on the intervention is obtained to assess the participants’ compliance with the intervention. If they do not submit their feedback, they will receive two reminders.

The following is the primary outcome:
Severity of PMS symptoms

The following are the secondary outcomes:
General self-efficacyQuality of working lifeThe effect of PMS on daily lifeCoping with premenstrual symptomsAnxiety and depression

### Data collection tools

A self-reported measure will be used for the purpose of data collection. Data will be gathered using a multi-part questionnaire that includes the following sections.

#### Demographic information

*Demographic information* will be examined using items such as age, marital status, level of education, height, weight, number of children, work experience, and type of employment.

#### Symptom diary to assess the severity of PMS

The severity of premenstrual symptoms was assessed based on the severity of 27 physical, and behavioral symptoms as well as 3 items related to interference with social activities were measured using a PMS symptom diary validated by Janda et al. [40] prospectively. Therefore, the participants will be requested to complete a daily prospective record of their symptoms during two consecutive menstrual periods using a 4-point Likert scale (0 = *normal*, 1 = *low*, 2 = *moderate*, 3 = *severe*). The effects of these symptoms on social aspects are examined. According to the DSM-V criteria for severe PMDD and PMS, a minimum of 5 symptoms (including a behavioral symptom) of the 27 primary items should be present (more than 2), with at least one of them related to the impact on social aspects (greater than 2) for no less than 2 days in the luteal phase [40].

For each woman, scores related to symptom severity (SI score) and severity of the interference with social activities (INT score) will be calculated. The first 27 items are used to calculate the SI score, and items 28 to 30 are used to calculate the INT score, which indicates social and occupational interference. These scores are calculated for the luteal phase. Luteal phase scores are calculated according to the last 7 days before menstruation. Only symptoms that are rated higher than or equal to 2 for at least 2 days will be entered into the calculation. The values of all items with a score greater than or equal to 2 for at least 2 days are added together and divided by 7 [40]. Therefore, the average severity of PMS symptoms per person will be calculated.

It should be noted that the symptom record sheet should be completed 2 months before the intervention starts, in order to diagnose PMS symptoms and assess the severity of PMS; the average of these 2 months will be considered as a baseline score. The severity of PMS will be assessed for 1 month immediately and 8 weeks after the end of the intervention to evaluate the short-term and long-term effects of the intervention.

#### Impact on everyday life and symptom intensity

This questionnaire was designed by Kues et al. in 2015. Its 18 items measure the impact of PMS on daily life through two subscales of psychological and functional effects. The validity of the measure was confirmed using exploratory factor analysis. Cronbach’s alpha coefficient of 0.9 for both subscales showed an acceptable level of reliability [41]. In the present research, this questionnaire has been translated into Persian, and its validity and reliability will be examined before the main study. This questionnaire will be completed before, immediately, and 8 weeks after the intervention.

#### Anxiety and depression

In the present study, the Hospital Anxiety and Depression Scale (HADS) will be used to assess anxiety and depression. This instrument was developed in 1983 by Zigmond and Snaith to screen for anxiety disorders and depression in non-psychiatric clinic patients. This scale comprises 14 questions in 2 subscales, namely, anxiety and depression. Each item is scored on a 4-point Likert scale ranging from 0 to 3. The maximum score that can be obtained for each subscale is 21. Scores above 11 on each subscale are considered abnormal, scores from 8 to 10 indicate borderline cases, and those from 0 to 7 are deemed as normal [42]. Bjelland et al. examined the psychometric properties of the HADS in a systematic review and concluded that it was an appropriate tool for assessing anxiety disorders and depression for different groups, including somatic patients, psychiatric patients, primary care clients, and the general population [43]. The psychometric properties of the Persian version were reviewed and confirmed [44]. This questionnaire will be completed before, immediately, and 8 weeks after the intervention.

#### Coping with premenstrual symptoms

The Premenstrual Change Coping Inventory is a self-report 17-item scale that measures individual strategies to deal with PMS. It includes three subscales, “seeking positive affect-inducing activities,” “seeking support,” and “healthcare use behavior” that are scored on a 4-point Likert scale from 1 (*not at all true*) to 4 (*totally true*). A higher score indicates a better status of coping with PMS [45]. In the present research, this questionnaire has been translated into Persian, and its validity and reliability will be assessed prior to the main study. This questionnaire will be completed before, immediately, and 8 weeks after the intervention.

#### The Work-Related Quality of Life Scale

The Work-Related Quality of Life Scale was first developed in England to assess the quality of occupational life in health care workers. Its validity and reliability were verified among medical personnel in the UK [46]. In the present research, this questionnaire has been translated into Persian, and its validity and reliability will be assessed prior to the main study. This questionnaire will be completed before, immediately, and 8 weeks after the intervention.

#### The General Self-Efficacy Scale

The General Self-Efficacy Scale was designed by Schwarzer and Jerusalem in 1995 to assess a person’s belief in their ability to respond to new or difficult situations and to deal with any obstacles and related problems. It consists of 10 items that are answered on a 4-point Likert scale ranging from “not at all correct” to “exactly correct.” Each person’s score is calculated as the average of the responses to all the questions [47]. A cross-cultural validation study using samples from 25 countries showed that this scale is unidimensional, having a Cronbach’s alpha of 0.75–0.91 [48]. This questionnaire will be completed before, immediately, and 8 weeks after the intervention.

### Timing of the outcome assessment

All outcome variables will be assessed before, immediately, and 7 weeks after the intervention (Fig. 2).

**Fig. 2 Fig2:**
[figure not shown]
Schedule of enrollment, interventions, and assessments

### Intervention fidelity

The second author is responsible for sampling and performing the intervention. However, the research group (specifically the last author) will supervise all stages of research implementation and content preparation.

### Data management

In this study, the data obtained from the questionnaires will be coded and entered into the SPSS software version 23. It should be noted that baseline data of all women identified as satisfying the eligibility criteria would be recorded initially. Data of discontinuing cases will be compared with the same data from those who agree to remain in the study. This will allow determining the representativeness of study subjects and generalizability of the finding. As mentioned above, this is an intervention study, and we did not find any adverse events for CBT in the literature; however, researchers plan is to report any unforeseen events or incidents during the study.

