**Methods/design:**

A randomized superiority controlled trial will be conducted involving 140 female employees of health centers affiliated with the Guilan University of Medical Sciences, Rudbar. The study involves a block size of 4 and 6 in a randomly varied order, 140 women who meet all the inclusion criteria will be randomly and equally divided into 2 groups: the intervention and the control groups. Those in the former group will receive a cognitive-behavioral therapy-based treatment for eight consecutive weeks on the social network platform WhatsApp; however, those in the control group will not be offered any treatment except usual care practices (unprotocolized usual care). The study’s primary outcome is the severity of PMS symptoms, and the secondary outcomes include general self-efficacy, work-related quality of life, the impact of PMS on daily life, coping with the symptoms, and experiencing anxiety and depression at the beginning of the study to identify people with PMS. A daily record of the symptoms will be completed for two consecutive months by all female employees aged 20–45 years who wish to participate in the study. According to the initial screening, those with moderate to severe PMS will be included. We will use the MLwin software for the analyses. All questionnaires will be completed by both groups immediately and 8 weeks after the termination of the treatment. The data will be analyzed using linear mixed-effects modeling with random intercepts and slopes.

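### The harms rule covers only unforeseen events that happen to surface and names no arm, so its event reports could neither be compared fairly between arms nor show that no harm occurred

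*Protocol article*

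**What the plan says.** The article's only harms statement is in Data management. It notes that "we did not find any adverse events for CBT in the literature" and then says that "researchers plan is to report any unforeseen events or incidents during the study". It gives no arm, no question and no schedule for this.

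Three other places bear on how an event would come to light:

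- **Intervention.** "Weekly feedback on the intervention is obtained to assess" compliance with the programme, which runs for eight weeks. "If they do not submit their feedback, they will receive two reminders". This is described only for women who receive the intervention. Per the abstract, control women receive unprotocolized usual care, and no weekly contact with them is described.
- **Abstract (Methods/design) and the diary section.** "All questionnaires will be completed by both groups immediately and 8 weeks after the termination of the treatment". For the diary, "The severity of PMS will be assessed for 1 month immediately and 8 weeks after the end of the intervention", with no restriction to one arm. The questionnaires include the HADS.
- **Sampling and randomization.** "blinding of study participants and outcome evaluators is almost impossible".

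Harms are not among the listed primary or secondary outcomes, and the data analysis section plans no harms analysis.

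**The concern.** Two separate weaknesses follow if the rule is applied as worded.

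The first is unequal ascertainment. Reports are left to surface by themselves, and one arm has a weekly line to the study team while the other has none described. With equal true event rates, more events would come to notice under CBT. In an unblinded trial nothing offsets this.

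The second is the reporting criterion. The most natural reading is that *unforeseen* governs both nouns that follow, so an event that could have been foreseen need not be reported. Even on a wider reading, nobody is asked. A short list of events, or an empty one, would then say little about whether harm occurred.

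This matters because the article hopes its findings will guide providers in choosing treatment. Any events that it reports are likely to be read by arm.

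**Working it through.** **What the plan gives.** It states no event rate, no detection rate and no harms sample size, so there is no figure of its own to reproduce and no bias that can be calculated from it. The steps below show what is already measured, then illustrate the possible size under stated assumptions.

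**Step 1: what is measured alike in both arms.**

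| Type of event | Described measurement after baseline | Same in both arms? |
|---|---|---|
| Worsening of PMS | Symptom diary, one month at each of two post-treatment times | Yes, no arm restriction stated |
| Anxiety, depression | HADS at both post-treatment times | Yes |
| Suicidal tendencies, new eating disorder, other health problems | None among the listed instruments; unsolicited report only | Not stated |
| Number of women who deteriorate | Data exist (diary, HADS), but the planned mixed model estimates effects and does not produce this count | Not planned |

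Suicidal tendencies and eating disorder serve as examples because both appear in the exclusion criteria. The article does not call them expected harms of CBT.

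**Step 2: contacts.** Intervention arm: 8 weekly feedbacks + 2 assessments = 10. Control arm: 2 assessments. Assume equal true event rates and the same chance *p* that an event is mentioned at each contact.

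**Step 3: all events occur before the first contact.** Share captured = 1 − (1 − p)^k, with k = 10 or 2.

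**Step 4: events spread evenly over 16 weeks.** This is 8 weeks of treatment plus 8 of follow-up, and only contacts after the event count. An event in treatment week w has (9 − w) feedbacks and 2 assessments left, so k = 11 − w, running from 10 down to 3. An event in weeks 9–16 has one contact left in either arm.

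- Intervention: ½ × mean of [1 − (1 − p)^k] over k = 3,…,10, + ½ × p
- Control: ½ × [1 − (1 − p)²] + ½ × p

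For p = 0.1: intervention ½ × 0.481 + ½ × 0.1 = 0.29; control ½ × 0.19 + ½ × 0.1 = 0.145; ratio 2.0.

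| p | Step 3: intervention vs control | Ratio | Step 4: intervention vs control | Ratio |
|---|---|---|---|---|
| 0.1 | 65% vs 19% | 3.4 | 29% vs 15% | 2.0 |
| 0.2 | 89% vs 36% | 2.5 | 47% vs 28% | 1.7 |
| 0.3 | 97% vs 51% | 1.9 | 58% vs 41% | 1.4 |

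The follow-up length is the 8 weeks of the abstract and instrument sections. The timing section gives 7 weeks and the analysis section 3 months. A longer follow-up gives more weight to the period in which the arms do not differ, so the Step 4 ratio falls.

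**Step 5: a second set of assumptions.** Let overall detection be 90% in the intervention arm and 90%, 50% or 30% in control. The ratio is 0.9/0.9 = 1.0, 0.9/0.5 = 1.8 or 0.9/0.3 = 3.0. At a true rate of 10% in 70 women per arm, expected reports are 70 × 0.10 × 0.9 = 6.3, against 6.3, 3.5 or 2.1.

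**Step 6: zero reports.** With complete detection, zero events in n women leaves a one-sided 95% upper limit of 1 − 0.05^(1/n). This is 4.2% for n = 70 and 4.6% for n = 63 (70 less 10% loss). It holds for any arm of this size and is not a defect of this plan. Incomplete detection means that an empty list excludes even less.

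**The case against.** The strongest reply is that no analysis is there to be biased. A reader might infer that the trial's harms comparison is biased, or that the authors mean to declare CBT free of adverse events. The documents support neither. They promise only to report events, and the literature remark says what was found, followed by an undertaking to report regardless. This stands: the problem is conditional on how the reports are used.

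A reader might also infer that deterioration will go unseen in both arms. That is wrong for the main examples, since PMS severity is the primary outcome and anxiety and depression are a secondary one, with the same schedule in both arms.

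Nor can unequal contact explain a false statement of no harm. Extra contact raises reported events under CBT. Only the narrow, unsolicited wording could lead to such a statement.

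Other parts of the reply stand in part:

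- Weekly feedback is for compliance and is not a stated harms channel. It is, however, the only described contact during treatment through which an event could be mentioned.
- Authors who foresee no adverse events may regard every event as unforeseen, and *incidents* may widen the rule. If so, the sentence is ambiguous and still needs rewording.
- Adverse event definitions and procedures are commonly left to a full protocol, which is not shown, so their absence here is no finding. The point rests on the criterion that the article does state.
- The independent audit under Ethical considerations covers all steps, including data, but is not described as collecting events from participants.
- The ratios are assumed. Step 3 gives every event all the contacts, which exaggerates. Counting the diary months as extra contact in both arms would bring the ratios closer to 1.

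**Conclusion.** The point holds in a limited form. The stated rule is narrow and passive, and it is silent on arm, while described contact during treatment is one-sided in an unblinded trial. Reports gathered this way should not be compared between arms, where they could overstate CBT harms, and should not be read as evidence of no harm.

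The gap is confined to events outside the diary and HADS and to the count of women who deteriorate. Its size cannot be derived from the article. The illustrated ratios, 1.4 to 3.4 with a per-contact chance of mention and 1.0 to 3.0 with assumed overall detection, depend on equal true rates and on detection rates that the documents do not give. The lower values go with events spread over follow-up or with detection equal in both arms. The primary efficacy analysis is not affected.

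**What to change.** 1. In Data management, make the reporting commitment cover *all adverse events, foreseen or unforeseen, in both arms*.
2. Add one open question, identical in both arms, to the questionnaire at the two existing post-treatment assessments: any new or worsened physical or mental health problem since the last assessment, with its date and any care sought.
3. Base any between-arm harms summary on that question alone. List events volunteered through weekly feedback separately, labelled as coming from a channel that only one arm has.
4. From data already collected, report by arm the number of women whose diary score or HADS subscale score worsened from baseline.

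The cost is one more question at two existing assessments, one descriptive table and a change of wording, with no added visits or staff. Reported event counts will be somewhat higher than under passive reporting. The article says that recruitment had not begun, so at that stage the change could apply to every participant.

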### Data analysis method

The effects of the intervention will be analyzed using a two-level linear mixed model in which repeated assessments will be time (variables from the beginning of the study to the end of the intervention and 3 months after its completion) at the first level and female employee at the second level. The model will be adjusted for the impact of potentially confounding variables (e.g., age, work experience). Mixed models are commonly used to handle missing data. Therefore, no additional steps will be taken to manage the missing data. Restricted iterative generalized least square estimation will be performed to produce unbiased estimates of the random parameters. The data will be analyzed by the intention to treat with the MLwiN 2.27 software.

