### Sample size estimation

The intervention effect will be evaluated by comparing the mean score of PMS symptom severity (primary outcome measure) between the two groups. Thus, the sample size was calculated based on the ability to detect a clinically relevant difference of 30% between the two groups in 8 weeks after intervention (30% reduction in the mean PMS score). This sample size accounted for a type I error rate of 0.05, any-pair power of 0.95, and all-pair power of 0.85. Based on the evidence from a previous study [39] and assuming a mean = 163.6, SD = 89.5, in group 1 and mean = 115.0, SD = 89.5, in group2 and an estimated reduction of 30% in the mean PMS score due to the intervention, the target sample size was calculated at 62 patients per group, with a 10% loss to follow-up, and to increase the power of the study, we selected 70 women in each group for a total sample size 140.

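### The random-slope model is not tied to the 8-week difference that sized the trial; if time is fitted as a straight line, it misstates the end-of-treatment effect and uses baseline inefficiently

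*Protocol article*

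**What the plan says.** **Model.** The Data analysis method section states: "The effects of the intervention will be analyzed using a two-level linear mixed model in which repeated assessments will be time". The outcome series there starts at the beginning of the study, so baseline is one of the responses. The abstract (Methods/design) gives the random part: "linear mixed-effects modeling with random intercepts and slopes".

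**Covariates.** "The model will be adjusted for the impact of potentially confounding variables (e.g., age, work experience" is followed by no mention of the baseline severity score.

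**Baseline.** Two monthly diaries are kept before treatment, and "the average of these 2 months will be considered as a baseline score" (Symptom diary section). Each post-treatment assessment is a one-month diary. The same section says the two post-treatment diaries are there to show short-term and long-term effects.

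**Target of the sample size.** The trial is sized to detect "a clinically relevant difference of 30% between the two groups in 8 weeks after intervention".

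**Follow-up time.** It is 8 weeks in the abstract, the sample size section and the diary section, 7 weeks under Timing of the outcome assessment, and 3 months under Data analysis method.

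**The concern.** A random slope needs numeric time, and with three occasions the natural reading is one straight line per woman and per arm, with the treatment effect taken from the group-by-time slope. The protocol's own account of CBT in the Introduction is different: the effect builds during treatment and lasts after the sessions end. That is a rise followed by a plateau, and a single slope cannot separate the short-term effect from the long-term one.

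Baseline as an unconstrained outcome also turns the contrast into a change score. Main effects of age and work experience do not alter a group-by-time contrast in complete, balanced data. The baseline symptom score, which is already collected and likely to be the best predictor of later scores, is not named for adjustment.

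At stake are a misstated end-of-treatment effect and precision given away on the primary comparison.

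**Working it through.** **1. The plan's own figure.** Inputs, from Sample size estimation: "assuming a mean = 163.6, SD = 89.5, in group 1 and mean = 115.0, SD = 89.5, in group2"; "This sample size accounted for a type I error rate of 0.05, any-pair power of 0.95, and all-pair power of 0.85"; and "the target sample size was calculated at 62 patients per group, with a 10% loss to follow-up".

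- Difference 163.6 − 115.0 = 48.6. Standardised: 48.6/89.5 = 0.543.
- A two-sided t-test at 0.05 with power 0.85 needs 61.9, so 62 per arm. The figure is reproduced, as a comparison of post-treatment means that makes no use of baseline.

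**2. Slope weights.** Assume linear time, a free group difference at baseline and complete data. The slope is Σ(t − t̄)y / Σ(t − t̄)². At weeks 0/8/16, t̄ = 8 and Σ(t − t̄)² = 64 + 0 + 64 = 128, so the weights are −8/128, 0, 8/128 = −0.0625, 0, +0.0625. End of treatment has zero weight.

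**3. What the line reports at 0/8/16.**

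| True group difference (baseline, end of treatment, follow-up) | Slope × 8 | Slope × 16 | Fitted lines at the three visits |
|---|---|---|---|
| 0, D, D | 0.50D | 1.00D | 0.17D, 0.67D, 1.17D |
| 0, D, 0 | 0 | 0 | 0.33D, 0.33D, 0.33D |

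With D = 48.6 and a sustained effect, the slope gives 24.3 at end of treatment. The fitted lines give 32.4 there and 56.7 at follow-up.

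**4. Dependence on the visit times (sustained effect).**

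| Weeks | Weights | Slope × (baseline to end of treatment) | Slope × whole span |
|---|---|---|---|
| 0/8/16 | −0.0625, 0, 0.0625 | 0.50D | 1.00D |
| 0/8/15 (the 7-week statement) | −0.068, 0.003, 0.065 | 0.54D | 1.02D |
| 0/8/21 (3 months read as 13 weeks) | −0.043, −0.007, 0.050 | 0.34D | 0.90D |
| −4/10/18 (diary mid-points, assumed) | −0.048, 0.008, 0.040 | 0.68D | 1.06D |

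Every reading understates the end-of-treatment effect.

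**5. Precision at follow-up.** Let rho be the correlation between baseline and follow-up. It is not in the document, so 0.4 to 0.6 is assumed, with equal variances. Relative to a post-treatment comparison (1), the variance is 2(1 − rho) for a change score and 1 − rho² with baseline adjustment. Their ratio is 2/(1 + rho). Power is two-sided at 0.05 from the noncentral t, with 62 per arm and standardised difference 0.543/√multiplier.

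| rho | Change: multiplier, power | Baseline-adjusted: multiplier, power | Ratio |
|---|---|---|---|
| 0.4 | 1.20, 0.78 | 0.84, 0.91 | 1.43 |
| 0.5 | 1.00, 0.85 | 0.75, 0.93 | 1.33 |
| 0.6 | 0.80, 0.92 | 0.64, 0.96 | 1.25 |

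The change score falls below the planned 0.85 only if rho < 0.5.

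**The case against.** The strongest reply is that the worst model is inferred. In a linear mixed model, linear names the model class, and a random slope describes the covariance. Categorical assessment effects can sit beside both. The article does not state the time coding, the interaction, a baseline group effect or the primary contrast, and a condensed article may leave these to a fuller document. This stands: everything computed from a straight line is conditional on that reading.

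A reader might go further and infer that zero weight on the middle visit spoils the planned 8-week comparison. The document does not support that. At 0/8/16, slope × 16 is exactly the difference in change from baseline to the visit that sized the trial. Under randomisation it is unbiased whatever happens at end of treatment, and only precision is lost.

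Nor is baseline as an outcome inefficient in itself. With the baseline means constrained equal and compound symmetry, the variance multipliers for the slope over 16 weeks are 0.85, 0.73 and 0.51 at rho 0.3, 0.5 and 0.7, close to the baseline-adjusted 0.91, 0.75 and 0.51. But with linear time that constraint gives the middle visit some weight, and a sustained effect is then read at follow-up as 1.13D, 1.09D and 1.05D. The constraint therefore works best with categorical time.

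Finally, the covariate list gives examples only, so adjustment for baseline is not ruled out, and the power loss rests on an undocumented rho. Both are fair. At rho 0.6 even the change score exceeds the planned power.

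**Conclusion.** The point holds in a limited form. The article commits to random intercepts and slopes with baseline among the outcomes, and does not tie that model to the 8-week difference or to the two separate effects it wants.

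- **Bias**, if time is linear with a free baseline difference, affects the end-of-treatment estimate (0.50D from the slope at 0/8/16) and the fitted group lines (0.67D and 1.17D). A benefit that has faded by follow-up gives a slope of zero, so a real short-term effect would go unseen in that contrast.
- **Precision** is what the planned 8-week difference loses: variance 1.25 to 1.43 times that of a baseline-adjusted analysis for the assumed rho of 0.6 to 0.4.

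The power figures assume equal variances, although baseline averages two cycles and each follow-up covers one. The weights depend on which follow-up time applies. The change is worth making because it costs almost nothing; the trial's primary comparison is not invalid as planned.

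**What to change.** In the abstract and in Data analysis method:

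- Enter assessment as a categorical factor with group-by-assessment effects.
- Use the baseline symptom severity (SI) score as a covariate, or keep baseline as an outcome with its means constrained equal across arms.
- Name the adjusted group difference at the 8-week follow-up as the primary effect, and report the end-of-treatment difference separately.
- An unstructured covariance is a suitable choice; it also allows baseline and follow-up variances to differ.
- Fix any further covariates in advance.
- Reconcile the follow-up times of 8 weeks, 7 weeks and 3 months.

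The cost is analysis wording and a few more covariance parameters, which 140 women can support. MLwiN can fit this as a multivariate response model. No extra data or participants are needed.
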